Even after successful microsurgical or endovascular treatment of the ruptured aneurysm, DCI is still a potentially devastating clinical syndrome related to aSAH and it is the most significant cause for morbidity and mortality in patients who survive the initial aSAH [1–3, 12]. DCI is a clinical syndrome of focal neurological and cognitive deficits presenting in about 30% of aSAH patients at 3–14 days after the initial insult, which might progress to infarction [1–5, 12]. While an angiographically evident vasospasm in the cerebral arteries can be detected in 70% of patients, less than half of them develop any symptoms or ischemia in the territory supplied by the narrowed artery [1]. In addition, treatment with the calcium-channel blocker, nimodipine, which is currently the standard of care and the only pharmacological intervention that has been shown to reduce the risk of DCI and improve neurologic outcome by one-third after aSAH, does not alter the incidence or severity of delayed cerebral artery vasospasm [13]. Furthermore, other clinical trials involving drugs that exert a significant impact on vasospasm did not have any impact on the risk of DCI or outcomes [1, 12, 14]. Consequently, recent research has questioned whether there is truly a direct causal relationship between cerebral vasospasm and DCI and it has been suggested that DCI following an aSAH is actually the result of a variety of different pathophysiological mechanisms, which are currently incompletely understood [1, 12, 15, 16]. From preclinical and clinical studies, a number of possible mechanisms other than vasospasm to explain the link between DCI and infarction have been proposed including microthromboembolism, cortical spreading depolarization and ischemia, microcirculatory dysfunction, inflammation, and impaired cerebral autoregulation [12]. It has been recommended that the main outcomes of clinical trials investigating strategies to prevent DCI should measure the extent of cerebral infarction by either radiologic imaging or autopsy biopsy as well as the patient’s functional outcome [17].

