#### Objectives

The primary objective is:

To explore whether xenon is neuroprotective in aSAH patients.

The secondary objectives are to explore the neuroprotective effects of xenon on:

The white matter injury in the cerebellum and corpus callosum. Recent studies have revealed that fractional anisotropy of white matter at 72 h post-SAH measured globally, in the cerebellum and in the corpus callosum, had an independent predictive value for both DCI and for a poor neurological outcome (i.e., mRS 3-6) [44].The incidence and severity of EBI within 72 h after the appearance of SAH symptoms, DCI, and cerebral infarction (according to a consensus statement [17] and consensus guidelines [5]: (1) DCI is defined as a new focal neurological deficit (such as hemiparesis, aphasia, apraxia, hemianopia, or neglect) or a decrease of at least 2 points in the Glasgow Coma Scale (either in the total score or in one of its individual components). This should last for at least 1 h and not be due to other causes (e.g., hydrocephalus, seizures, metabolic derangement, infection, sedation). DCI is not apparent immediately after aneurysm occlusion and cannot be attributed to other causes by means of clinical assessment, CT or MRI scanning of the brain, and appropriate laboratory studies; (2) cerebral infarction is defined as a new infarct on follow-up imaging (i.e., in any of the following: 2nd MRI, CT, CTA, DSA, and perfusion CT) between day 4 and 6 weeks after the initial appearance of SAH symptoms.The incidence of adverse events, serious adverse events, suspected unexpected serious adverse reactionsThe inflammatory process, i.e., assessed by the extent of microglial activation and the levels of cytokine in cerebral spinal fluid (CSF)The need and duration of intracerebral pressure (ICP) treatmentsPlasma catecholamine levelsThe release of troponin TThe release of neuron-specific enolase (NSE), neurofilament light (NF-L), glial fibrillary acidic protein (GFAP), calcium-binding protein S100B (S100B), ubiquitin carboxyterminal hydrolase L1 (UCH-L1), total tau, and cytokines (tumor necrosis factor alpha, interleukins 6 and 10)

The exploratory objectives are:

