To explore the predictive value of the different MRI techniques (see details under the section of “Data collection and management”) alone and combined for clinical outcome at 3 months, and also at 1 and 2 years after SAH.To examine the pathophysiological pathways of the post-SAH period between the two treatment groups and to assess the predictive value of selected proteomics and metabolomics on severity of EBI and DCI and neurological outcome (i.e., good outcome: mRS 0–2 vs poor outcome: 3–6)To evaluate the role of microglial activation (see details under the section of “Data collection and management”) on the development of DCI.To explore the role of the cytokine level on the development of DCITo assess a combination of selected brain imaging markers obtained from different MRI techniques (see details under the section of “Data collection and management”), biomarkers (see secondary objectives # 8), plasma metabolomics (see details under the section of “Data collection and management”), CSF metabolomics and clinical examinations (e.g., motor score, pupillary light reflex with pupillometry, epileptic seizures) as a prognostication model for EBI, DCI, and neurological outcome at 3 months, at 1 and 2 years after SAH (i.e., good outcome: mRS 0–2 vs poor outcome: 3–6).To test the applicability of utilizing a brain network analysis with graph theoretical analysis and anatomical connectivity of white matter tracts (see details under the section of “Data collection and management”) in prognostic models for EBI, DCI, and neurological outcome at 3 months, at 1 and 2 years after SAH (i.e., good outcome: mRS 0–2 vs poor outcome: 3–6) and to investigate xenon’s effect on the connectivity.To unravel the mechanisms underpinning the development of EBI and DCI by utilizing brain imaging obtained from different MRI techniques (see details under the section of “Data collection and management”) and metabolomics (i.e., plasma and spinal fluid; see details under the section of “Data collection and Management”)To measure the clinical neurological outcome at 3 months and at 1 year and at 2 years.To develop a prognostication model for EBI and DCI and neurological outcome at 3 months and at 1 year and at 2 years after SAH

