### Secondary outcome measures

Fractional anisotropy of white matter at cerebellum and/or at corpus callosum as assessed with the 1st MRI.Safety and tolerability of xenon, as assessed with a ratio of adverse events, serious adverse events, and suspected unexpected serious adverse reactions (SUSARSs) during the follow-up at 1 year between the xenon group and the control group.Composite of radiological EBI (within 72 h after the start of SAH symptoms), DCI, cerebral infarction (see definitions in detail under the section of secondary objectives) and poor outcome (good: mRS 0–2; poor: mRS 3–6) at 3-months and at 1 year.Neurogenic stress cardiomyopathy and stunned myocardium (i.e., myocardial injury caused by sympathetic storm and autonomic dysregulation with hs-troponin elevation, left ventricular dysfunction or ECG changes)ICP-level up to 14 days (i.e., as long as clinically relevant) after the onset of aSAH symptomsNeed for ICP therapies up to 14 days (i.e., as long as clinically relevant) after the onset of aSAH symptomsDuration of therapy for ICP control/monitoring up to 14 days (i.e., as long as clinically relevant) after the onset of aSAH symptomsPlasma catecholamine levelsDifference in selected biomarkers (NSE, NF-L, GFAB, S100B, UCH-L1, total-tau TNF-α, interleukins 6 and 10) and difference in metabolomic and lipidomic profiles in the blood and CSF between xenon and control group in predicting risk for EBI, vasospasm, DCI as well as a good neurological outcome at 3 months, 1 year, and at 2 years after the aSAH.Development of prognostication models with a selected combination of brain imaging and biomarkers obtained from various MRI techniques (see details under the section “Data collection and management”), clinical data, and metabolomics (see details under the section “Data collection and management”) by applying artificial intelligence and machine learning for EBI, vasospasm, DCI, and a good neurological outcome at 3 months, 1 year, and at 2 years after the aSAH.Difference in CTA, DSA, and MRI parameters obtained from various MRI techniques (see details under the section “Data collection and management”) between xenon and control group in predicting EBI, vasospasm, DCI, and a good neurological outcome at 3 months, 1 year, and at 2 years after the aSAH.Predictive value of computational fluid dynamics (CFD) (see details under the section “Data collection and management”) to detect the differences in the blood flow behavior in the recruited patients by applying 3D DSA to assess the risk of EBI within the first 72 h after the start of aSAH symptoms, vasospasm (within 21 days after the start of SAH symptoms) and DCI (between day 4 and 6 weeks after the start of SAH symptoms) and a good neurological outcome at 3 months, at 1 year, and at 2 years after the aSAH (mRS 0–2).Difference of metabolomics and lipidomics profiles of plasma and CSF between xenon and control group and in predicting the risk for EBI within the first 72 h after the start of aSAH symptoms, vasospasm (within 21 days after the start of SAH symptoms) and DCI (between day 4 and 6 weeks after the start of SAH symptoms) and a good neurological outcome at 3 months, at 1 year, and at 2 years after the aSAH (mRS 0-2).Difference of activity of microglial cells between the subjects in the xenon and control groups and in predicting the risk for DCI and a good neurological outcome at 3 months, 1 year, and at 2 years after the aSAH.

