The following MRI techniques will be used: (1) T2-weighted and fluid-attenuated inversion recovery (FLAIR) sequences; (2) T1-weighted 3D gradient echo sequence for volumetric analysis; (3) time of flight angiography (TOF) to visualize flow within vessels, without the need to administer a contrast agent; (4) brain perfusion imaging with dynamic susceptibility contrast (DSC), (5) a susceptibility-weighted imaging (SWI) sequence to image hemosiderin, (6) whole-brain (and region-of-interest level) white matter integrity from diffusion-weighted MRI data measured with diffusion tensor imaging (DTI; fractional anisotropy is the primary end-point of the current trial; (7) voxel-wise white matter microstructure from diffusion-weighted MRI data. A global voxel-wise data-driven Tract Based Spatial Statistics (TBSS) with DTI and other microstructural metrics will be applied; (8) constrained spherical deconvolution (CSD) technique will be used to estimate the orientation of multiple fiber populations, e.g., crossing fibers, in a voxel accurately and within a clinically feasible scan time. The fiber orientation distributions will be estimated with CSD and used to perform probabilistic fiber tractography for the whole brain and for certain tracts of interest. The whole brain tract networks will be analyzed with graph theoretical analysis [49–53].

In addition, all feasible patients (i.e., capable to co-operate adequately during the scan) will be scanned in the Turku PET Centre. The 1st scan will be performed 4 ±1 weeks after the onset of SAH symptoms with the 2nd scan being undertaken at 3 months after the onset of SAH symptoms. It will be explored whether [^11^C](R)-PK11195 can be used to test the hypothesis that xenon can exert a neuroprotective effect and to explore the role of inflammatory process in the extent of DCI and also the neurological outcome at 1 year after SAH. We postulate that this can be demonstrated by showing less signs of microglial activation in the xenon-treated group than in the reference therapy group and in the patients with good outcome, i.e., mRS 0–2 [54–56].

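### Microglial PET is listed as predicting DCI, but the first scan comes after the period in which the protocol says DCI presents, so the DCI part of this outcome cannot support a prediction or causal claim

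*Protocol article*

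**What the plan says.** - **Aim.** Secondary outcome measures, last item: "Difference of activity of microglial cells between the subjects in the xenon and control groups and in predicting the risk for DCI". The same item adds good neurological outcome at 3 months, 1 year and 2 years. It gives no time window for DCI.
- **Related objective.** Among the exploratory objectives: "To evaluate the role of microglial activation" in the development of DCI, with the reader sent to the data collection section for the method.
- **Measurement.** Plans for assessment and collection of outcomes {18a} describes one microglial measure, a PK11195 PET: "The 1st scan will be performed 4 ±1 weeks after the onset of SAH symptoms". One repeat is planned, at 3 months.
- **Who is scanned.** Same section: "all feasible patients (i.e., capable to co-operate adequately during the scan) will be scanned in the Turku PET Centre".
- **When DCI occurs.** Background and rationale {6a} describes DCI as "presenting in about 30% of aSAH patients at 3–14 days after the initial insult". The computational fluid dynamics item and the separate metabolomics and lipidomics item of the secondary outcomes instead write "DCI (between day 4 and 6 weeks after the start of SAH symptoms". The secondary objectives use the same span for cerebral infarction, "between day 4 and 6 weeks after the initial appearance of SAH symptoms", but attach no days to their definition of DCI.

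**The concern.** A predictor has to be measured before the event it predicts, in people who have not yet had that event. Here the document fixes both the scan date and the predictive aim, and on the background section's timing they are in the wrong order. An association between PET signal and DCI could then mean that DCI provoked the microglial activation, and the scan cannot separate this from activation contributing to DCI.

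The scanned set is also selected. Patients enter intubated, with Hunt-Hess grade 3 to 5. Those who have died or are too impaired to co-operate at 3 to 5 weeks are not scanned, and these plausibly include some of the worst DCI cases. Membership of the PET set may therefore depend on the outcome being predicted.

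At stake is how one secondary outcome and one exploratory objective can be reported: a correlation found after the event could be presented as prediction or as a step in the development of DCI.

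**Working it through.** None of the protocol's own calculations bears on this point. The check is a comparison of dates, followed by a rough count of events.

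**Inputs**
- First PET: 4 ± 1 weeks = 28 ± 7 days = days 21 to 35 (section {18a}).
- Second PET: 3 months (same section).
- DCI period A: days 3 to 14, in about 30% of patients (Background and rationale).
- DCI period B: day 4 to 6 weeks = days 4 to 42, a span of 42 − 4 = 38 days (two items of Secondary outcome measures).
- Enrolment: 80 per group, 2 × 80 = 160 (Sample size {14}).

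**Step 1: period A.** The gap from the end of the period to the scan is 21 − 14 = 7 days at the earliest and 35 − 14 = 21 days at the latest. The whole period has passed before any scan.

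**Step 2: period B.** Share elapsed = (scan day − 4) / 38; days left = 42 − scan day.

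| First PET on day | Elapsed | Days left |
|---|---|---|
| 21 | 17/38 = 45% | 21 |
| 28 | 24/38 = 63% | 14 |
| 35 | 31/38 = 82% | 7 |

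No patient is scanned before this window opens: the earliest scan is 21 − 4 = 17 days into it.

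**Step 3: second PET.** Three months lies beyond day 14 and beyond day 42, so this scan follows DCI under either period.

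**Step 4: events.** Assume that the 30% quoted for aSAH patients in general applies to this trial. Expected DCI is 0.30 × 160 = 48 patients.
- Under period A, 0 of the 48 events follow a scan.
- Under period B, suppose events are spread evenly over the 38 days. This is generous, because the background section places them early. Events after the scan would be 48 × 21/38 = 26.5 for a scan on day 21, 48 × 14/38 = 17.7 on day 28 and 48 × 7/38 = 8.8 on day 35.

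The period B counts cover everyone enrolled. The scanned set is smaller, by an amount that the document does not give. With the protocol's own description of timing, the number should lie near the lower end, at few or none.

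**Step 5: what the timing leaves intact.** The xenon-control comparison of PET signal needs no order relative to DCI. The first PET precedes the functional assessments at 3 months, 1 year and 2 years. The second PET coincides with the 3-month assessment and precedes only the later two.

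**The case against.** The strongest reply is that days 3 to 14 is a description from the literature in the rationale, not the trial's outcome window, and does not say that DCI never presents later. Where the outcomes list gives DCI a window, it runs to 6 weeks and the first scan lies inside it. This stands, and it limits the point. A reader might infer that predicting DCI from PET is ruled out altogether, but the document does not support that: under the wider window a small, late part of DCI could still be predicted.

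It can also be said that only one clause of the item is affected, that the data collection section speaks more loosely of exploring inflammation's role in the extent of DCI, which an association could meet, and that modelling detail belongs in a fuller document. The first two stand. The third does not rescue the clause: the scan date and the predictive aim are both stated here, and no model can put the scan ahead of DCI that has already happened.

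Two further inferences are tempting and fail.
- One is that the case for xenon's mechanism collapses. The protocol rests that on less activation in the xenon arm and in patients with good outcome, not on the PET-DCI association.
- The other is that every predictor in the trial must precede the opening of its outcome window. That would bar much of the first MRI (72 ± 24 h) from predicting DCI, and the 24 to 72 h biomarkers from predicting early brain injury, and nothing here supports it.

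Finally, the selection effect is disclosed as a feasibility limit, and neither its direction nor its size can be worked out from the document.

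**Conclusion.** The point holds for the DCI part of the microglial outcome and for the matching exploratory objective. As written, the predictor is measured 7 to 21 days after the period in which the background section says DCI presents. Under the wider window it is measured with 45% to 82% of that window gone. The analysis can show an association. It cannot support a claim that microglial activation predicts DCI or contributes to it, except for any late DCI in patients still free of it at the scan.

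This rests on PET being the only microglial measure, since the article describes no other, and on DCI following roughly the timing given in the background. If much DCI arose after week 3, more could be predicted, but the item would still need the restriction to patients free of DCI at the scan. The primary outcome, the sample size and the randomised comparisons are not touched. It is worth correcting because a listed secondary outcome does not fit its own measurement schedule and the remedy is nearly free.

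**What to change.** In the last secondary outcome and the exploratory objective on microglial activation, do one of the following:
1. Recast the DCI part as an association: PET signal as the outcome, with treatment and prior DCI as explanatory variables.
2. Keep prediction, but count only DCI arising after the scan, in patients free of DCI at the scan.

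Option 1 uses all scanned patients; option 2 is likely to have very few events. Under either, state that results apply to patients able to undergo the scan.

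Use the second PET only for outcomes assessed after it, namely function at 1 and 2 years. Keep the first PET as a predictor of function at 3 months, 1 year and 2 years. Reconcile the DCI timing in the background section with the window in the secondary outcomes, and state one window for the microglial item.

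The cost is a change of wording. One predictive claim is given up or narrowed; the scan schedule is unchanged.

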
## Participant timeline {13}

The schedule of events for study participants, including enrolment, interventions, and assessments, is outlined in Fig. 1.

**Fig. 1 Fig1:**
[figure not shown]
Participant timeline

## Sample size {14}

A sample size of 100 is estimated on the basis of recent studies in aSAH patients as being able to provide 80% power with a 2-sided α level of 0.05 in order to detect a mean difference of 0.02 (SD 0.035) in the global fractional anisotropy of white matter between the xenon-treated group and the control group [44]. In addition, this mean difference is estimated to have a predictive value for DCI and poor neurological outcome. It is estimated that approximately 30% of the enrolled patients will be lost from the MRI studies, and therefore, 80 patients per group will be enrolled in this study.

## Recruitment {15}

A team of anesthesiologists and neurosurgeons at each study site will be responsible for setting up and organizing the swift identification of potential SAH patients that arrive in the emergency department and they will have a contingency plan in place to ensure equally rapid screening for eligibility, obtaining of written consent and recruitment.

The primary recruitment center for the start of this study will be Turku University Hospital; the other centers are expected to join after the feasibility of the protocol has been assured. The expected rate of recruitment is 20 patients, consisting of both the Xenon-intervention arm and standard-of-care arm, per year at Turku University Hospital. Tampere University Hospitals expected rate of recruitment is comparable to Turku, with 20 patients per year. Kuopio University hospital’s rate of recruitment is expected to be 10 patients per year. Thus, the expected recruitment phase of the study is expected to last 4 years.

## Assignment of interventions: allocation

### Sequence generation {16a}

After screening, an eligible patient will be included in the study and randomly allocated into either the standard of care arm or the xenon intervention arm in a ratio of 1:1. Informed written consent of participation will be received from the next of kin or the legal representative of the included patient as soon as possible. Trial sites will have access to an Internet-based randomization system. Each subject will be assigned a unique study and randomization number. A block randomization approach will be stratified by the study site.

### Concealment mechanism {16b}

Randomization will be Internet-based, and the use of a validated password website will ensure concealment.

### Implementation {16c}

The Xe-SAH -trial comprises the following scheduled events: screening, ICU stay (treatment induction and maintenance and post-treatment), hospital stay after ICU stay, and follow-up at 3, 12, and 24 months after the SAH. In order to confirm the feasibility of the protocol (i.e., period of feasibility), the trial will be initiated in the intensive care unit of Turku University Hospital in close liaison with the Departments of Neurosurgery and Neuroradiology. We expect that the period of feasibility will be completed within 3–6 months. Thereafter, the trial will also be started in Tampere and Kuopio University Hospitals. Implementation will be the responsibility of the senior physicians and researchers from the Departments of Anesthesiology and Intensive Care, Neurosurgery, and Neuroradiology at each participating center.

